### Secondary end points

The secondary end points (see Table 1) include for both arms:

**Table 1 T1:** Study design

Inclusion Criteria:	Exclusion Criteria:
Elective planned CABG surgery	Emergency revascularization: patients with hemodynamic instability or requiring inotropic or intra-aortic balloon support

First isolated CABG surgery	Previous cardiac surgery

Adult patients (18 years and older) and competent to give informed consent	Planned concomitant valve surgery

	Bad varicous veins

	Previous safenectomy

	History of deep vein thrombosis

	History of suffered trauma on the lower extremity

	Preoperative legs immobilization

	Previous leg wound complications

	Coexisting illness with life expectancy < five years

• identification of predictors for a possible development of a harvest-site complication: preoperative demographics such as sex, obesity, diabetes, peripheral vascular disease and operative demographics such as EVH vs. CVH approach, number of bypass grafts, time on bypass, harvest site (below or above the knee), characteristics of the bandage will be considered and analyzed;

• evaluation of differences between EVH and CVH in operative time, mobility time, number of medications, hospital length of stay, readmission for leg wound complications or need for outpatient wound management resources and generally in all resources that need to be allocated;

• Evaluation of differences between EVH and CVH in the quality of the harvested venous conduits;

• Comparison of health-related quality of life (EUROQol-5D) and leg pain score and identification of factors, in addition to treatment allocation, that are associated with variations in quality of life outcomes.

• correlation of the long-term outcome with the vein histological scores determined at harvest time.

For the EVH arm only:

• effect of the harvest site, whether below or above the knee;

• effect of the vein preparation solution;

• effect of an uncontrolled distension pressure or no touch technique on vein patency and long-term outcomes;

• assessment of systemic carbon dioxide absorption.

ESOS is meant to be an interventional, single centre, prospective randomized study with an all-comers design. Each cohort will initially be formed by 115 patients. This number has been selected to balance statistical requirements and resource limitations.

In the course of the trial all consecutive adult patients (18 years and older) with elective planned and first isolated coronary artery disease (CAD) amenable to coronary artery bypass grafting surgery will be screened to establish their eligibility to both EVH and CVH on the basis of the guidelines reported in Table 1.

Patients not amenable for both treatment options, or who are expected to have a better outcome with one of the two, will not be included in the trial; neither will be the patients who refuse to be randomized because of their personal preference for one approach over the other.

Patients deemed amenable for both harvesting modalities, after having signed the informed consent, will be assigned by means of a standard web-based computer generated randomization scheme to one of the two cohorts, either EVH or CVH, and after allocation they will be included in the intention to treat analysis. An independent clinical research assistant will be responsible for randomization and treatment assignment.

The post surgery follow-up will consist of clinic visits on the sixth week after CABG surgery and at occurrence of any adverse event. Each information leading to in-patient or out-patient treatment regarding major adverse cardiac events, vein-graft failure or occlusion or other morbidity, will be collected. The number of visits required to clear up each wound complication will be used as a surrogate to determine outpatient resource utilization for wound management.

Follow-up angiograms will be performed at 18 months to explore directly vein graft longevity. This will allow not to rely totally on the indirect, and sometimes deceiving, information supplied by the event-free survival rates.

Follow-up will stretch over a minimum of 24 months. At the end of this period there will be an assessment of the state of the art based on the results obtained with the two different approaches, whose rationale will lead to the decision to either conclude or continue the follow-up.

### Trial Population, and Statistical Analysis

To assess accurately the trial, the study investigators have followed the CONSORT 2010 checklist with methodological rigour [20].

Study recruitment has initiated in August 2010. Figure 1 illustrates the planned study flowchart, and Table 1 reports its details.

**Figure 1 F1:**
[figure not shown]
**Flowchart of the study design**. This figure illustrates the study design.

All data relative to enrolled patients will be entered in a database containing preoperative demographics and risk factors (age, sex, BMI, morbidities, coronary artery lesions severity by SYNTAX score and surgical risk profile by EUROscore, etc), intra-operative variables (site of harvesting, number of incisions, lengths, times, etc), vein specific variables, pre- and post- harvesting respiratory and hemodynamic parameters, histological status of the harvested vein, as examined and graded by a pathologist. Wound healing and variables in the ASEPSIS score and other wound-related morbidities, wound complications, outcome and correlated events of the follow-up are to be evaluated by an independent clinical committee every 6 weeks in the first year, and then at 18 and 24 months. The total number of data characterizing each patient will be approximately 180, a complete scenario of his risk factors, surgical and post surgery history, short-, mid- and long-term outcome. The two cohorts will hence be described by two 115 × 180 arrays, with the intention to bring to light differences and similarities in behaviors and trends by means of a thorough statistical analysis.

The continuous data will be reported as average ± standard deviation and will be analyzed by standard ANOVA tests. Discrete or dichotomous values will be reported as percentages, risk ratios (and their 95% confidence intervals), and will be stratified in *mxn *contingency tables, analyzed for significant differences by chi-square tests (with Yates'correction in the case of 2 × 2 tables) and Fisher or mid-P tests.

The freedom from late wound complications and in general all event-free survival rates will be obtained according to the Kaplan-Meyer method, with the statistical differences among them estimated by the Mantel-Cox log-rank test. As usual, statistical significance will be determined at a *p *value (probability of null hypothesis: the observed differences are imputable to chance) ≤ 0.05, corresponding to the false positive probability (α or type I error). In case of a *p *value > 0.05, the next step will be the estimate of the test power *II *and the related false negative probability (β or type II error = 1- *II*).

A few considerations on the selected sample size are opportune. Assuming the values conventionally accepted for the drop-out and cross-over rates of ≤ 10% and ≤ 5% of the patients, follow-up will see two cohorts of approximately 100 patients for each. This means that data computed as percentage within each cohort should be correctly reported with an uncertainty of ± 5%.

It is well known that the power of the statistical test used to carry out comparisons between two sets of data depends both on the sample sizes and the entity of the difference between data observed in the two groups. A tiny difference has difficulty to be evidenced as statistical significant even with a very large sample size, while a substantial difference can be easily assessed as significant even with a small sample size.

In a trial in which the analysis wants to take into account several outcomes, the presence of a wide range of observable differences makes very difficult a "valid-for-all" estimate of the sample size necessary to achieve the desired test power (usually 80%) or inversely on the test power predicted on the base of the actual sample size.

In our trial, as far as the short-term outcome is concerned, previous studies [8,9] suggest a six-week leg wound complication rate of about 20% in the CVH arm and less than 4% in the EVH arm. With this risk/prevalence difference of 16%, and the predicted sample size of 100, the power based on normal approximation is about 94% (91% if we apply the continuity correction), and thus very good: a power of about 80% would be reached already with a sample size around 80.

The situation changes dramatically when we consider the mid- and long term outcomes. Previously quoted studies [2] suggest a first-year vein-graft failure rate of about 20% with an annual occlusion rate of 1% to 2% in the first six years, with practically no difference between the EVH and CVH approaches. On the basis of previous comparative trials of EVH versus OVH, none of the clinically relevant cardiovascular outcomes differed significantly for EVH compared with OVH (Allen et al. [11] reported survival free of MACE at up to 5 years as 75% vs. 74%, p = 0.85). A 2-3% of non-inferiority margin is therefore planned in this protocol study. The 80% test power goal, with such small risk prevalence difference requires sample sizes of at lest 3000 for each cohort, values well beyond any practical implementation in a single medical centre, at least in a lifetime.

On the basis of these considerations, the initial recruitment number of 115 patients per cohort, with end-point number of about 100 patients, sustainable from the point of view of human and financial resources, looks fully acceptable.

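### The single ANOVA rule for continuous data, on its usual reading, leaves the pairing and the pre-harvest value of the before/after readings unused; naming a paired and a baseline-adjusted analysis is a minor, free improvement

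*Protocol article*

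**What the plan says.** All of this is in the protocol article.

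- Trial Population, and Statistical Analysis (text after Figure 1): the database is to hold "pre- and post- harvesting respiratory and hemodynamic parameters", so each such parameter is read twice in the same patient.
- Same section: continuous data are summarised as mean and standard deviation and "will be analyzed by standard ANOVA tests". No paired test, change score, repeated-measures model or baseline adjustment is named anywhere in the article.
- Same section: significance is declared at a p "value (probability of null hypothesis: the observed differences are imputable to chance) ≤ 0.05". A larger p value is to be followed by an estimate of the test's power.
- Secondary end points: "assessment of systemic carbon dioxide absorption" is listed under "For the EVH arm only", so no contrast between arms is planned for it. No measure or test is attached to it.
- Sample size: "Each cohort will initially be formed by 115 patients", and after losses "follow-up will see two cohorts of approximately 100 patients for each".

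**The concern.** Ordinary ANOVA assumes independent observations and has no place for a baseline value. Two readings on one patient are usually positively correlated. The rule can then fall short in two ways.

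1. **Between arms.** If only post-harvest values are compared, the pre-harvest value, which explains part of the variance, goes unused. The comparison is unbiased but less precise than it could be.
2. **Within an arm.** If pre and post values are entered as two independent groups, the standard error of the change is too large, and a real change is harder to detect.

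The second case matters most where there is no comparator arm. The CO2 item is such a case, if it is to be answered from these readings. A method that makes a finding of no change more likely suits that question poorly.

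**Working it through.** **The plan's own figure.** The only power calculation concerns wound complications: a "six-week leg wound complication rate of about 20% in the CVH arm and less than 4% in the EVH arm", with 100 per arm. Pooled rate 0.12; null SE √(2·0.12·0.88/100) = 0.0460; alternative SE √((0.16 + 0.0384)/100) = 0.0445. Power = Φ((0.16 − 1.96·0.0460)/0.0445) = 94.2%. Subtracting 1/100 from the difference as a continuity correction gives 91.1%. The stated 94% and 91% are reproduced, which indicates a two-sided 5% level. These figures say nothing about the before/after readings.

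**Inputs for this point.** The article gives no SD, effect size or pre-post correlation for these parameters. The correlation ρ is therefore an assumption, shown from 0 to 0.7, with equal SDs before and after. Normal approximations are used. A test with 80% power has an expected z of 1.96 + 0.84 = 2.80.

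**Within an arm.** The variance of the mean change is 2σ²(1−ρ)/n; the independent-groups analysis takes it as 2σ²/n.

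- SE inflation: 1/√(1−ρ)
- True level: 2·(1 − Φ(1.96/√(1−ρ)))
- Power where the paired test has 80%: Φ(2.80 − 1.96/√(1−ρ))

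**Between arms.** ANCOVA has residual variance σ²(1−ρ²).

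- Power of post-only ANOVA where ANCOVA has 80%: Φ(2.80·√(1−ρ²) − 1.96)

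| ρ (assumed) | SE inflation | True level, unpaired | Power, unpaired (paired 80%) | Power, post-only (ANCOVA 80%) |
|---|---|---|---|---|
| 0 | 1.00 | 5% | 80% | 80% |
| 0.3 | 1.20 | 1.9% | 68% | 76% |
| 0.5 | 1.41 | 0.6% | 51% | 68% |
| 0.7 | 1.83 | 0.03% | 22% | 52% |

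For ρ = 0.5: 1.96/√0.5 = 2.77, so Φ(2.80 − 2.77) = 51%; and 2.80·√0.75 = 2.43, so Φ(2.43 − 1.96) = 68%.

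**At the trial's size.** The table fixes the effect where the better test has 80% power, so the sample size cancels. With 100 patients in one arm and a fixed within-patient shift, the paired test has power Φ(δ/√(2(1−ρ)/n) − 1.96), and the independent-groups test truly has Φ((δ/√(2/n) − 1.96)/√(1−ρ)), with δ in SD units:

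| Shift | ρ = 0.3: unpaired / paired | ρ = 0.5 | ρ = 0.7 |
|---|---|---|---|
| 0.25 SD | 41% / 56% | 39% / 70% | 36% / 90% |
| 0.40 SD | 85% / 92% | 89% / 98% | 94% / 99.9% |

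Between arms, with 100 per arm and a difference of 0.3 SD, post-only ANOVA has 56% power at any ρ. Change scores have 43%, 56% and 78% at ρ = 0.3, 0.5 and 0.7. ANCOVA has 60%, 69% and 84%. ANCOVA beats both in every case, which is why it is the form to name.

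**The case against.** The strongest objection is that the error is not in the text. A reader might infer that the trial will treat two readings on one patient as two patients. The article does not say so: ANOVA on change scores and repeated-measures ANOVA are both forms of ANOVA, and neither is excluded. The data are described as one array per cohort, 115 patients by about 180 values, in which pre and post readings sit naturally as two columns of one patient's row. The stated aim is to compare the two cohorts. A condensed article may also leave such detail to the full protocol or analysis plan. All of this stands, and it limits the point to what the named method does on its usual reading.

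It is also right that ANOVA of post-harvest values between randomised arms is valid; preferring ANCOVA there is a matter of efficiency.

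A further tempting inference is that a true rise in CO2 would be reported as no absorption. The article does not support it. It never says that the respiratory readings serve the CO2 item, and it plans a power estimate after a non-significant result, which is an imperfect safeguard but not a flat claim of absence.

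What remains is that the section is specific elsewhere (Yates, Fisher or mid-P, log-rank), yet names one method without exception for continuous data, including variables that it describes as measured before and after. A better method is available from readings already planned.

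**Conclusion.** The point holds as a minor improvement to the analysis of secondary parameters. Between arms, the named method is valid but less efficient than ANCOVA for any non-zero correlation. Within an arm, an independent-groups comparison would be conservative for any positive correlation; whether one is intended is left open.

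The size depends on assumed correlations and shifts and cannot be fixed from the article. The within-arm loss is large for small shifts with a correlation of about 0.5 or more. At 0.4 SD it is at most about 9 percentage points for the correlations shown, with power still 85% or higher. Neither the six-week wound end point nor the two-year cardiac end point is touched.

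**What to change.** Add to Trial Population, and Statistical Analysis, after the rule for continuous data, wording to this effect:

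*Parameters measured before and after harvest are compared between arms by ANCOVA of the post-harvest value on arm and pre-harvest value, and reported as an adjusted mean difference with 95% CI. Changes within an arm are analysed as paired differences, with the mean change, SD of change and 95% CI. Standard ANOVA is kept for variables measured once.*

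If the CO2 item is to be answered from these readings, say so there; the paired-difference rule then applies to it. If the full protocol or analysis plan already specifies this, a cross-reference is enough. The cost is a few lines of wording: no extra measurements, patients or visits.

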### Primary end points

We have two primary end points (see Appendix 1) with different deadlines:

• a short-term one (6 weeks after CABG surgery), regarding freedom from wound complications, defined as cellulitis, edema, ecchymosis, hematoma, cellulites, drainage, necrosis, dehiscence, debridement; leg wound infection according to ASEPSIS score;

• a long-term one (2 years after CABG surgery), regarding freedom from MACE, i.e. death, myocardial infarction, recurrent angina or congestive heart failure due to vein graft failure with assessment of vein-graft patency.

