### Conventional harvesting

Conventional vein harvesting will be performed through longitudinal incisions over the course of the saphenous vein (SV), starting at the medial malleolus. The length of the incision will depend on the amount of vein required (at least a minimum of 18-20 cm per each vein segment). The incisions will be closed in layers, with absorbable subcutaneous and subcuticular sutures. Elastic bandage wrapping or support stockings will be used in all patients, until up to at least 72 hours after harvesting. 

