### Endoscopic vein harvesting

A 2,5 cm longitudinal incision will be made in the thigh above the knee (two finger-breadths posterior to the medial edge of the tibia). After initial identification of the saphenous vein, a plane of dissection along the anterior surface of the vein will be performed using as endoscopic dissector the Sorin ClearGlide, an open CO2 EVH system. This device is not dependent on gas insufflation to maintain tissue separation and/or the tunnel. The insufflator of the endoscopic-tower is capable to regulate the gas flow and maintain a zero gradient pressure in the cavity. A low flow of CO_2 _is required (4 l/min) to flush the working channel and optimize the vein exposure.

Vein harvesting will be initially directed proximally until 2 cm below and lateral to the pubic tubercle, where the SV enters the cribriform fascia (*fascia lata*) to join the femoral vein. Then, depending on the amount of vein required, distal (below the knee) harvesting may be extended until the medial malleolus. Branches will be divided using an electrothermal bipolar tissue-sealing cautery (Ligasure™ 5 mm Laparoscopic Instrument Valleylab). SV will be divided distally to initial incision using endoclips (Endosurgery) and endoforceps (SorinGroup), and a small stab incision will be made to pull the vein.

The incision will be closed with absorbable subcutaneous and subcuticular sutures, starting after reversal of the heparin infusion. Elastic bandage wrapping or support stockings will be used in all patients, up to at least 72 hours after harvesting.

After harvesting, the vein will be cannulated and prepared with papaverine and heparinised blood, and branches will be ligated using titanium clips or/and 3-0 silk ties.

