### Histology

A first check on the validity of the endoscopic device (given for granted the surgeon's ability) may be furnished by the histological evaluation of specimens collected during the harvest, with the assessment of the level of disruption in the various layers of the venous wall. Absence, or minimal presence of disruption should constitute a good start for a satisfactory vein outcome.

The uniformity, continuity, and integrity of vein structures will be assessed by histological studies conducted in a blind fashion by two of the authors ([name] and [name]), who will evaluate the vein histological structures according to the so-called "Griffith score" [21] which estimates the percent disruption of each histological structure (see Table 2).

**Table 2 T2:** Histology Grading

The histological structures to be evaluated are the:	**The numeric grading system estimates the percent disruption of each histological structure and will be scored according to the following scale **[2]:	
*endothelial layer*	0	Intact or not disruption

*elastic lamina*	1	< 10%

*medial smooth muscle and connective tissue*	2	10-25%

*adventitial connective tissue*.	3	25-50%

	4	> 50%

At this purpose it is important to point out that the results obtained on the specimens collected during the learning curve are very encouraging: the average overall score is 0.3 ± 0.6 over a total of 4.0, with a flat "zero" (intact structure) for the medial connective tissues, medial smooth muscles and adventitial connective tissues.

Another open issue is whether the vein preparation procedure might influence SV histology. As now, there is no standard vein-preparation solution used in clinical practice [22,23]. The authors will investigate whether the preparation solution and a controlled distension pressure or no touch technique might prevent histological disruption and influence vein patency and long-term outcomes. (Appendix 1)

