## List of abbreviations used

ESOS: Endoscopic saphenous harvesting with an open CO_2 _system; CABG: Coronary artery bypass grafting; CAD: Coronary artery disease; PCI: Percutaneous coronary intervention; EVH: Endoscopic vein with open CO_2 _harvesting; CVH: Conventional vein harvesting; SV: Saphenous vein; MACE: Major adverse cardiovascular events: death; myocardial infarction; revascularization (PCI or CABG) for ischemia or angina recurrence; GF: vein-graft failure at least 75% of stenosis at angiographic study; GO: vein-graft occlusion

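### One committee evaluates both the arm-revealing leg wounds and the follow-up outcomes, and no blinding is stated for cardiac events or angiograms

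*Protocol article*

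**What the plan says.** All references are to the protocol article.

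- **Who evaluates.** Under Trial Population, and Statistical Analysis (text below Figure 1), a single sentence begins with "Wound healing and variables in the ASEPSIS score and other wound-related morbidities" and goes on: "wound complications, outcome and correlated events of the follow-up are to be evaluated by an independent clinical committee every 6 weeks in the first year". It then adds 18 and 24 months.
- **What the leg shows.** Conventional harvesting: "Conventional vein harvesting will be performed through longitudinal incisions over the course of the saphenous vein (SV), starting at the medial malleolus". Endoscopic vein harvesting: "A 2,5 cm longitudinal incision will be made in the thigh above the knee", plus a small stab incision.
- **The 2-year primary end point.** Primary end points gives freedom from MACE as "death, myocardial infarction, recurrent angina or congestive heart failure due to vein graft failure with assessment of vein-graft patency". List of abbreviations used gives a different content: "Major adverse cardiovascular events: death; myocardial infarction; revascularization (PCI or CABG) for ischemia or angina recurrence". The same list defines vein-graft failure as a stenosis of at least 75% at angiography.
- **Angiograms.** Follow-up angiography takes place at 18 months. The reader is not named.
- **Where blinding is stated.** Only under Histology: vein structure "will be assessed by histological studies conducted in a blind fashion by two of the authors".

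**The concern.** Independence protects against a conflict of interest. It does not hide the allocation. A body that evaluates a patient's leg wound will in the ordinary course learn which harvest technique was used, because a long incision along the vein and a short incision with a stab wound are described and scored differently. The article gives that same body the follow-up outcomes.

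Much of the long-term primary end point needs clinical judgement. An adjudicator must decide whether chest pain is recurrent angina, whether heart failure is present, and whether the event came from a failed vein graft. If the arm is known, a borderline event can be counted in one arm and set aside in the other. A larger sample does not remove that error. Leg wounds are hard to assess blind, but clinical event files can be reviewed without leg data. The article already specifies blind reading for histology, which is a secondary outcome.

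**Working it through.** **1. Is there a figure in the plan to reproduce?** None bears on adjudication. The stated power for the 6-week wound end point (20% v 4%, 100 per arm) reproduces at 94.2%, or 91.1% with continuity correction, against 94% and 91% in the article. This point does not change it.

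**2. Exposure of each component, passages side by side.**

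| Component | Where it stands | Judgement needed |
|---|---|---|
| Death | both definitions | none if all causes count; attribution if the graft-failure qualifier applies |
| Myocardial infarction | both | limited; attribution if the qualifier applies |
| Recurrent angina | Primary end points | yes |
| Congestive heart failure | Primary end points only | yes, with attribution to the graft |
| Revascularization for ischemia or angina | abbreviations only | yes, on the indication |
| Graft failure (75% stenosis or more) | abbreviations | reduced by a measurable threshold |

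In Primary end points it is unclear whether the graft-failure qualifier covers every component or only the last. The abbreviations list has no such qualifier. The reach of the causal call is therefore uncertain, which itself leaves the adjudicators more discretion.

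**3. Assumed number of events.** The article gives no 2-year rate. It cites event-free rates of 75% and 74% at five years and 80% and 83% at three years. Under an assumed constant hazard, the 2-year risk is 1 − S^(2/t):

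- 1 − 0.75^(2/5) = 10.9%
- 1 − 0.74^(2/5) = 11.3%
- 1 − 0.80^(2/3) = 13.8%
- 1 − 0.83^(2/3) = 11.7%

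That is about 11 to 14 events per 100 patients. The cited rates are not restricted to graft-attributed events, so the number under the stricter reading would be lower.

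**4. Effect of re-classification.** With about 100 patients per arm, one event moved in one arm changes the difference by 1/100 = 1 percentage point.

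**5. Effect of arm-dependent attribution (illustration).** Let the true risk be r in both arms, and let the share attributed to the graft be 10 points higher in one arm. The spurious difference is 0.10 × r:

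- r = 11% to 14%: 1.1 to 1.4 points
- r = 17% to 25% (the cited 3- to 5-year levels, taken as a high case): 1.7 to 2.5 points. With 50% to 70% attributed in the other arm, the two-sided rejection rate rises from 5% to about 6.5% to 8%.

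**6. Scale for comparison.** The standard error of the difference is √(2p(1−p)/100): 4.4 points at p = 11% and 4.9 points at p = 14%. The 95% half-width is 1.96 times that, about 8.7 to 9.6 points.

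**The case against.** Several readings go further than the document allows.

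- **That adjudication is unblinded.** A reader might infer this. The article says neither blinded nor unblinded, and a condensed article may leave adjudication procedure to the full protocol or a committee charter. This stands against calling it a stated fact. It does not remove the point, because the article does fix the joint task, and where it mentions blinding it does so only for a secondary outcome.
- **That the committee has looked at the legs.** The text says the items are evaluated, shortly after describing the database. Clinic visits are scheduled only at week six and at adverse events, so evaluation every six weeks may well be record review. Records would still tend to disclose the arm: the database holds harvest site and the number and length of incisions. Nor does the article say that the same members handle both tasks.
- **That the causal call governs the whole end point.** The abbreviations list carries no such qualifier, and the 75% threshold limits discretion on the graft itself. It does not settle whether a symptom was caused by that graft. The appendix cited for the end points is not in the text at hand.
- **That bias would consume the 2-3% non-inferiority margin.** Moving 2 to 3 of 11 to 14 events means re-classifying 14% (2/14) to 27% (3/11) of one arm's events in one direction. Nothing in the document supports such a rate. The article also concedes that a difference of this size needs at least 3000 per cohort, so the trial cannot test that margin anyway.
- **That hope for the endoscopic technique drives the adjudication.** The hope in the Discussion is the authors'. The committee is described as independent.
- **That masking is simple.** Titanium clips are among the branch-ligation options in the endoscopic section, and the conventional section is silent on branches. Visible clips could reveal the arm on an angiogram. Committee size is not given.

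**Conclusion.** The concern holds in limited form. As written, the design gives arm-revealing wound evaluation and follow-up outcomes to one committee, and no text separates the tasks or blinds the cardiac and angiographic assessment. The judgement-dependent components of a primary end point are therefore open to arm-aware classification. All-cause death and the 75% stenosis criterion are less exposed.

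No estimate of bias follows from the document. The only sizing available is about 1 percentage point per re-classified event, on an assumed 11 to 14 events per 100 under a constant hazard. That is small beside the sampling error of the long-term comparison, but sampling error is no reason to leave an avoidable bias in place. The point is a worthwhile low-cost improvement. It does not invalidate the trial, and no sample-size figure changes.

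**What to change.** In Trial Population, and Statistical Analysis, state that:

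1. Cardiac events and their attribution to graft failure are adjudicated from coded files with harvest technique, leg findings and operative notes removed.
2. The adjudicators are existing committee members who do not evaluate that patient's wounds.
3. The 18-month angiograms are read under coded identifiers against the 75% criterion, noting that visible clips may limit masking.
4. Wound assessment is unblinded.

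Reconcile the MACE content in Primary end points with that in List of abbreviations used, including which components the graft-failure qualifier covers, so that the adjudicators apply one definition.

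The cost is a few sentences, preparation of masked files, and allocation of tasks within the committee. The committee must be large enough to divide the work, which the article does not show. No extra patients or procedures are needed.

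### Neither stated analysis route (mean ± SD with ANOVA, or unordered tables) suits the ordered 0-4 histology grade; a minor point affecting secondary end points only

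*Protocol article*

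**What the plan says.** The protocol article, in the section on trial population and statistical analysis, gives two rules for outcomes that are not time-to-event:

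- For continuous outcomes: "The continuous data will be reported as average ± standard deviation and will be analyzed by standard ANOVA tests".
- For the rest: "Discrete or dichotomous values will be reported as percentages, risk ratios (and their 95% confidence intervals), and will be stratified in" m × n tables, tested by chi-square (Yates-corrected when 2 × 2) and by Fisher or mid-P tests.

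It names no median, rank test, transformation or ordinal model, and does not say which rule covers the histology grade.

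The outcomes concerned are listed under Secondary end points: "Evaluation of differences between EVH and CVH in the quality of the harvested venous conduits", and "evaluation of differences between EVH and CVH in operative time, mobility time, number of medications, hospital length of stay". The Histology section uses a grade "which estimates the percent disruption of each histological structure". Table 2 codes it 0 for intact, then 1 to 4 for under 10%, 10-25%, 25-50% and over 50%. For the learning-curve specimens, "the average overall score is 0.3 ± 0.6 over a total of 4.0", with zero throughout for the medial and adventitial structures.

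**The concern.** The histology grade is ordered, bounded at zero and coded from bands of unequal width. Under the continuous rule, a step from intact to slight disruption counts the same as a step from 25-50% to over 50%, and the mean ± SD summary describes a symmetric spread that cannot exist near the floor. Under the discrete rule, the test ignores that grade 3 is worse than grade 1. The article therefore offers two routes, and both use the data poorly.

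At stake is the comparison of conduit quality, which the Histology section treats as an early check on the endoscopic device. With about 100 patients per arm there is little power to spare. Length of stay, mobility time and medication counts raise a related question, because such outcomes often have a long right tail.

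**Working it through.** **Inputs from the protocol article.** At analysis "follow-up will see two cohorts of approximately 100 patients for each"; alpha is 0.05; the histology score is 0.3 ± 0.6 on a 0-4 scale. No power is stated for any continuous or ordinal end point, so there is no figure on this point to reproduce.

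**Convention check.** The one stated power, for wound complications at 20% v 4%, reproduces with a two-sided 5% test and 100 per arm. Pooled rate: (0.20 + 0.04)/2 = 0.12.
- Uncorrected: z = [0.16 − 1.96·√(2·0.12·0.88/100)] / √[(0.20·0.80 + 0.04·0.96)/100] = (0.160 − 0.090)/0.0445 = 1.57, power 94%.
- Continuity-corrected: subtracting 1/100 from the difference gives z = 1.35, power 91%.

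I used the same alpha, sidedness and sample size below.

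**Step 1: the summary.** Mean − SD = 0.3 − 0.6 = −0.3, below the scale minimum of 0. The SD is twice the mean.

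**Step 2: a matching distribution (assumption).** I took one grade per patient, with probability of grade k proportional to exp(ak + bk²), and chose a and b to give mean 0.3 and SD 0.6. The probabilities are 0.762, 0.187, 0.041, 0.008 and 0.001 for grades 0 to 4, with skewness about 2.2. Check of the mean, using four decimals: 0.1867 + 2·0.0413 + 3·0.0083 + 4·0.0015 = 0.30.

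**Step 3: power for histology.** The other arm is shifted by a proportional odds ratio (OR). For example, at OR 2 the odds of grade 0 fall from 0.762/0.238 = 3.2 to 1.6, so its probability becomes 0.62. Results from 10,000 simulated trials:

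| OR | Wilcoxon | ANOVA | Unordered chi-square | Loss, ANOVA | Loss, chi-square |
|---|---|---|---|---|---|
| 1 (null) | 4.8% | 4.9% | 3.4% | – | – |
| 1.5 | 24.9% | 23.0% | 14.0% | 2 | 11 |
| 1.75 | 43.9% | 40.1% | 27.0% | 4 | 17 |
| 2.0 | 62.3% | 57.3% | 42.7% | 5 | 20 |
| 2.4 | 83.6% | 79.0% | 66.1% | 5 | 18 |
| 2.5 | 86.9% | 82.9% | 70.3% | 4 | 17 |

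A second set of grade probabilities (0.765, 0.18, 0.045, 0.008, 0.002; mean 0.302, SD 0.611) gives 84%, 79% and 64% at OR 2.4, so the chi-square loss there is about 20 points. A further run with grades matched to 0.3 ± 0.6 gave 62%, 57% and 41% at OR 2.0, a loss of 21. Part of the chi-square loss comes from sparse high grades, which make that test conservative. Fisher and mid-P versions were not simulated.

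**Step 4: times and counts.** The article gives no mean, SD or range for these, so the shape is wholly assumed. I used a log-normal distribution with a shift of 0.4 log-SD:

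| Log-SD | Ratio of medians | Wilcoxon | ANOVA | Loss |
|---|---|---|---|---|
| 0.3 | 1.13 | 78% | 78% | 0 |
| 0.5 | 1.22 | 78% | 75% | 3 |
| 0.7 | 1.32 | 79% | 71% | 8 |
| 0.9 | 1.43 | 79% | 65% | 14 |
| 1.0 | 1.49 | 79% | 61% | 18 |

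Losses are taken before rounding. In a separate run of 8,000 trials at log-SD 0.3, 0.5, 0.7 and 1.0, ANOVA's type I error was 4.6% to 5.1%.

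**The case against.** The case for leaving the plan alone is reasonable, and much of it stands.

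- Both primary end points are event outcomes, analysed by contingency tables or Kaplan-Meier and log-rank methods. Nothing here touches them.
- The ANOVA rule is written for continuous data, and the article does not say that the histology grade falls under it. This stands, but the alternative route is the worse of the two for an ordered grade.
- The 0.3 ± 0.6 is an average overall score from a learning-curve series of 20 endoscopic patients, with no conventional arm. The SD may be pooled over layers and specimens, and a score averaged over layers takes more than five values. The simulated sizes are therefore illustrative.
- An unseen analysis plan may add distribution checks or rank tests. The article, however, states a method that fits this end point badly, which goes beyond leaving detail out.
- For resource use and cost, the mean is a legitimate target, and a rank test answers a different question. This also stands.

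A reader might infer that length of stay and mobility time are known to be strongly skewed and that ANOVA will lose much of its power on them. The documents give no distribution for either, and under mild skew the loss is 0 to 3 points. A reader might also infer that a few extreme patients could produce false positive findings. The simulations show no inflation of type I error. Finally, the planned correlation of histology with long-term outcome is a separate analysis that the ANOVA sentence does not govern.

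**Conclusion.** The point holds in a limited form and is minor. For the histology grade, the protocol article's own scale and learning-curve result show a floor-bound, skewed, ordered outcome that neither stated route handles well. Against a rank test, the cost is about 2 to 5 points of power under ANOVA and about 11 to 21 under unordered chi-square. This assumes one grade per patient matched to 0.3 ± 0.6, a proportional-odds shift and 100 per arm.

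For length of stay, mobility time and counts, skewness is likely but undocumented. In the log-normal cases the loss runs from 0 to about 18 points, depending entirely on the skew assumed. That justifies a supplementary analysis and does not support a claim that the planned one is invalid.

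**What to change.** Amend the statistical section, or state in the analysis plan, as follows:

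- **Histology grade:** say which rule applies and whether the unit is a grade per structure or an overall score per patient. Report the distribution of grades by arm, or median and quartiles for an overall score. Compare arms with a Wilcoxon/Mann-Whitney test or a proportional-odds model.
- **Length of stay, mobility time and counts:** add medians with quartiles and a rank, log-scale or count-model analysis. Keep the difference in means for the resource and cost comparison.
- **Roughly symmetric measures:** keep mean ± SD and ANOVA.

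The cost is wording only, with no extra patients or data. The small downside is that a rank-test effect is not a difference in means, so both must be reported where cost is the question.
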